#### Target trial emulation using observational data from TriNetX and CPRD

*Eligibility criteria*. Anonymised, person-level, electronic health data will be extracted from TriNetX and CPRD, linked across primary care, ED, inpatients, outpatients, and mortality subsets. The study period will be from 01/01/2014 to 01/01/2024. Included will be men and women aged 16–54 years. The study will take an open cohort design with patients entering the cohort when the following criteria are met:

Either: ≥1 epilepsy disease or symptom code recorded during the study period and two separate valproate prescription instances over the preceding 12 months before at least one of the epilepsy disease or symptom codes;

Or: ≥1 epilepsy disease or symptom code recorded any time before the study period with at least two separate valproate prescription instances over 12 months during the study period.

TriNetX and CPRD use ICD-10-CM and SNOMED codes, respectively. The coding strategy combining disease and symptom codes with valproate, as used our published study successfully [20], was shown to accurately identify epilepsy cases in our prior work [28,29].

Treatment arms:

Withdrawn valproate and commenced lamotrigineWithdrawn valproate and commenced levetiracetamWithdrawn valproate and no new ASM commencedContinues valproate

*Treatment assignment*. Baseline (time 0) will be defined as when valproate dose reduction commences (treatment arms 1–3) or prescription of valproate at a matched time (arm 4). Eligible individuals are assigned at baseline to the treatment strategy that their data are consistent with [21]. To emulate randomisation, adjustment is made for baseline confounders using Robins’ generalised methods (g-methods, e.g., inverse probability weighting) [21], considering age, sex, ethnicity, deprivation, type of epilepsy (using G40 codes), baseline seizure frequency (symptom codes recorded over preceding 12 months), alcohol excess, developmental delay, Cambridge Multimorbidity Score, length of valproate treatment, valproate dose, and ASMs used other than valproate. The final set of covariates required to adjust for confounding will be chosen using a causal directed acyclic graph [21].

*Outcomes*. These are listed in the target trial design section and derived from our prior work [1,20,30,31], and public consultation. All coded events will be recorded for flexible categorical or continuous analyses, as needed.

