*Causal estimand*: Assesses impact of treatment arms 1–3 vs. 4 on outcome (per-protocol assumption as observational data limits ITT assessment) [21].

*Start and end of follow-up*. The start of follow-up (Time 0 or index date) will be defined as when valproate treatment discontinued (treatment arms 1–3) or prescription of valproate at a matched time (arm 4). For time-to-first-event analyses, the end of follow-up will be defined as when the outcome occurs, censoring (including deviation from assigned treatment or leaving the study catchment area), or 10 years. For recurrent events analyses, alongside censoring as above, the end of follow-up will be 10 years, allowing for all events to be assessed throughout follow-up.

*Statistical analysis*: mirrors target trial section.

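### Time zero for the three withdrawal arms is defined both as the start of dose reduction and as discontinuation, so the taper may or may not be part of follow-up

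*Protocol article*

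**What the plan says.** All the relevant text is in the protocol article, in the section on target trial emulation using TriNetX and CPRD data.

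- Treatment assignment: "Baseline (time 0) will be defined as when valproate dose reduction commences (treatment arms 1–3").
- Start and end of follow-up: "The start of follow-up (Time 0 or index date) will be defined as when valproate treatment discontinued (treatment arms 1–3").
- Arm 4 has the same wording in both places, "or prescription of valproate at a matched time (arm 4"), so its date depends on whichever definition is used for arms 1–3.
- Assignment rule: "Eligible individuals are assigned at baseline to the treatment strategy that their data are consistent with". Arms 1–3 are labelled as valproate withdrawn with lamotrigine commenced, levetiracetam commenced, or no new antiseizure medication (ASM) commenced.
- Cohort entry: "The study will take an open cohort design with patients entering the cohort when the following criteria are met". The first route needs a code in the study period and "two separate valproate prescription instances over the preceding 12 months before at least one of the epilepsy disease or symptom codes". The second needs an earlier code and "at least two separate valproate prescription instances over 12 months during the study period". Neither is tied to time zero.
- One of the adjustment variables is "baseline seizure frequency (symptom codes recorded over preceding 12 months"), a window whose position moves with time zero.

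**The concern.** Both sentences use the time 0 label for the same arms, so they cannot be read as two deliberate landmarks. Two analysts following the two paragraphs would build different cohorts with different follow-up and different baseline covariates.

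The taper is a period in which harm from withdrawal could first appear. The target trial described under Aim 1 randomises people who are taking valproate, so events during the taper would count in it. The example question for the Aim 2 model is asked when withdrawal is being proposed, so its answer should also include the taper. A clock that starts at discontinuation serves neither purpose. Under Pathways to impact, the Aim 1 figures are intended for the section of the NHS England decision tool that tells patients about risks to themselves.

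**Working it through.** **1. The two readings side by side**

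*Time zero at discontinuation.* Events between first reduction and stopping fall before follow-up. A patient who dies in the taper, or goes back to continuing valproate, never reaches time zero and is not in arms 1–3. Arm 4 has no corresponding lost period. Seizure codes from the taper also fall in the 12-month window for baseline seizure frequency, so part of the effect of withdrawal would be adjusted away. All of this lowers the apparent early harm of withdrawal.

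*Time zero at first dose reduction.* Taper events count. However, completed withdrawal, and a new ASM if it starts after the first reduction, are only known later. If patients were placed in arms by that later information, those in arms 1–3 would have had to survive to the point that defines the arm. Separately, the first eligibility route does not say that the qualifying code must come before time zero, and seizure symptom codes are also an outcome.

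**2. The plan's own figure**

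Table 1 gives p1 = 2977/8021 = 0.3712 (withdrawn) and p2 = 2471/8021 = 0.3081 (continued) for ED attendance. The coded formula is n = (z_0.975 + z_0.80)² × [p1(1−p1) + p2(1−p2)] / (p1−p2)². It returns 881, as stated. That figure is not in dispute; the same inputs are used below.

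**3. How much could fall in the gap (illustration)**

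Inputs from Table 1: withdrawn-arm risk 0.3712 and a pilot follow-up of 5 years. Assumed, because the article does not give them: a taper of 1, 3 or 6 months, and a hazard during the taper of 1, 2 or 3 times the pilot value.

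Withdrawn-arm hazard = −ln(1 − 0.3712)/5 = 0.0928 per year.

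Share with a first ED attendance in the gap = 1 − exp(−0.0928 × k × m/12), for m months and multiplier k:

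| Taper | k = 1 | k = 2 | k = 3 |
|---|---|---|---|
| 1 month | 0.8% | 1.5% | 2.3% |
| 3 months | 2.3% | 4.5% | 6.7% |
| 6 months | 4.5% | 8.9% | 13.0% |

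First-year risk at constant hazard is 1 − exp(−0.0928) = 8.9%. With no rise in hazard, the gap therefore holds about 9%, 26% or 51% of first-year first ED events for tapers of 1, 3 or 6 months. As a share of five-year first events it holds 2%, 6% or 12%.

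**4. Size of the conditional risk under the dose-reduction reading**

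Suppose arm membership did require an event-free taper of T years, followed to F years. With no true effect, the rate ratio would be roughly 1 − T/F. Computed with the continued-arm hazard, −ln(1 − 0.3081)/5 = 0.0737 per year, it is 0.91, 0.75 and 0.50 at one year for 1, 3 and 6 months, and 0.98, 0.94 and 0.89 at five years. This applies directly to death. For non-fatal events it is the extreme case, because a patient can have the event and still complete withdrawal.

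**The case against.** The contradiction itself has no good defence, but several stronger readings are tempting and the article does not support them.

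- *Immortal time is built in.* A reader might infer this from assignment at baseline to the strategy the data fit. That wording is also compatible with cloning or a grace period. The article names g-methods and censors at deviation from assigned treatment. A grace-period rule is detail that an article commonly leaves to a fuller document. It also gives no order for the new ASM and the first reduction; if the new drug is already prescribed, the arms can be partly told apart at time zero. What stands is a risk that the wording permits.
- *The first eligibility route selects withdrawn patients on the outcome.* Patients enter when criteria are met and only eligible individuals are assigned, so the natural reading is that eligibility comes first. The order is loose, not wrong.
- *Arm 4 is restricted to people who later stay on valproate.* Nothing says so. It is defined by a prescription at a matched time, with deviators censored.
- *The gap could swallow the powered difference.* It is tempting to set 6.7% (3 months, tripled hazard) beside the pilot difference of 37.1% − 30.8% = 6.3 points. The first counts all first events in the gap in one arm, the second is a difference between arms. The excess over an unchanged hazard is 6.7 − 2.3 = 4.4 points, and it rests on an assumed tripling. ED attendance is also planned as a recurrent-events outcome, so a taper visit does not remove later ones.
- *The bias cannot be undone.* The data are retrospective and access is still being sought, so index dates can be redefined.

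It is also fair to say that where valproate is stopped abruptly the two dates coincide.

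None of this reconciles the two definitions, and an unseen analysis plan can follow only one of them.

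**Conclusion.** Wrong as written. The article defines one time zero in two incompatible ways, and no other part of it settles which applies. This rests on the text alone and is certain.

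The discontinuation reading understates early harm of withdrawal. The amount depends on taper length and hazard, neither of which the article gives: about 0.8% to 13% of withdrawn patients with a first ED attendance in the gap, for tapers of 1–6 months at one to three times the withdrawn-arm pilot hazard. That range is illustrative and is not an estimate of bias in any planned effect measure.

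Immortal time under the dose-reduction reading, and a qualifying code that falls after time zero, are points to close off in the wording. They are not errors the article commits.

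**What to change.** - Use one time zero in both paragraphs, the first valproate dose reduction, and replace the discontinuation definition under Start and end of follow-up. This is an analytic index date and implies nothing about how valproate should be withdrawn. It fits both the target trial and the Aim 2 question. It needs dose to be recorded, which the plan already expects because valproate dose is a listed confounder.
- Start follow-up on that date in arms 1–3 and on the matched date in arm 4, and end the baseline covariate windows there.
- Require all eligibility criteria to be met on or before time zero.
- For patients compatible with several arms at time zero, name a method that does not assign by later data. Cloning with censoring and weighting, or sequential trials, would each do, with a grace period that the authors choose and justify.

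The cost is revised wording, more programming and somewhat wider confidence intervals from any added weighting. No new data are needed, and data access was still being sought when the article was written.

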### Addressing Aim 1: Target trial emulation

#### Target trial design

A hypothetical target trial will be emulated in which young men and women taking valproate would be randomised to either continue valproate, switch to lamotrigine or levetiracetam, or discontinue valproate [21]. The following mortality and morbidity outcomes would be assessed over the subsequent five years:

Deaths (all-cause/epilepsy-related);ED/hospital admissions (all-cause/epilepsy-related);Seizures (symptom codes);Falls;Injuries;Burns;Aspiration pneumonia;Manic/bipolar episodes;New-onset depression;Self-harm/suicide;A composite morbidity index incorporating seizures, injuries, admissions, depression.

Intention-to-treat (ITT) and per-protocol effects would be assessed between groups [21]. Analysis would take a time-to-first-event approach (Cox-proportional hazards model) for deaths, new-onset depression and composite morbidity. A recurrent events approach (e.g., Prentice-Williams-Peterson Total Time Model) would be taken for the remaining outcomes.

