### Addressing Aim 2: Causal prediction modelling

A causal prediction model will be created using Cox-proportional hazards of time-to-first-event in a causal framework [26]. The predicted outcome will be a composite personal harms risk combining epilepsy-related deaths, seizures, injuries, admissions, and depression. Predictors for definite inclusion in the final model will be treatment arms 1–4. Candidate predictors considered in addition will be taken from the list of baseline confounders adjusted in the target trial emulation, alongside any additional variables considered to influence outcome but not treatment assignment. *A priori* clinical expertise and data-driven variable selection will refine the predictor variable list for modelling [30]. Penalisation methods (e.g., *lasso*), will be used to combine variable selection with shrinkage (reducing overfitting risks).

The model will be developed in TriNetX to help ensure it is internationally generalisable [32]. External validation will be undertaken in CPRD, facilitating subsequent clinical implementation [32]. Internal validation within TriNetX will involve 1,000 bootstrap analysis samples. Nagelkerke’s R^2^ and Brier Scores will estimate overall model performance. Calibration will be estimated with calibration-in-the-large, calibration slope, and flexible calibration plots, and discrimination with C-index. Calibration and discrimination will be reassessed within CRPD to externally validate model performance [32]. Counterfactual prediction will be embedded into the model development [26], allowing patients and clinicians to answer clinically meaningful questions such as “at the point of proposed valproate withdrawal, accounting for baseline characteristics, what is the risk of epilepsy-related death or composite morbidity for levetiracetam? And what is it for lamotrigine?”

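### Time 0 for the two switch arms depends only on valproate, so where the new drug is started first, its introduction falls before follow-up and patients who abandon it never enter a switch arm

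*Protocol article*

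**What the plan says.** All places are in the protocol article.

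- **Target trial design.** In the hypothetical trial, "young men and women taking valproate would be randomised to either continue valproate, switch to lamotrigine or levetiracetam, or discontinue valproate". Assignment happens while everyone is still on valproate.
- **Treatment arms.** Arms 1 and 2 are people who came off valproate and started lamotrigine or levetiracetam. Arm 4 is people who continue valproate. Nothing bars an arm 4 patient from having started one of the two drugs.
- **Treatment assignment.** "Baseline (time 0) will be defined as when valproate dose reduction commences (treatment arms 1–3"), and "Eligible individuals are assigned at baseline to the treatment strategy that their data are consistent with". Other antiseizure drugs appear only among the baseline confounders: "valproate dose, and ASMs used other than valproate". Baseline seizure frequency is taken from codes in the preceding 12 months.
- **Start and end of follow-up.** "The start of follow-up (Time 0 or index date) will be defined as when valproate treatment discontinued (treatment arms 1–3"). This is a different date from the one under Treatment assignment. Follow-up ends at the outcome, or at "censoring (including deviation from assigned treatment or leaving the study catchment area), or 10 years".
- **Causal estimand.** Arms 1–3 against arm 4, with a "per-protocol assumption as observational data limits ITT assessment".
- **Aim 2.** The model is to give the risk on each drug "at the point of proposed valproate withdrawal, accounting for baseline characteristics".

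**The concern.** Time 0 should be the moment at which the strategies diverge. For a switch, that can be the first prescription of the new drug, because a patient may start it while valproate is unchanged. Neither stated date is tied to that event.

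Two things follow where the new drug comes first. For patients who go on to reduce valproate, events during the introduction of the new drug are not outcomes. Seizures in that window can instead enter the baseline seizure count, and the new drug itself can enter as a baseline covariate. Patients who abandon the new drug and never reduce valproate do not reach time 0 of arm 1 or 2 at all, and can still qualify for arm 4.

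What is at stake is the question answered. When withdrawal is proposed, nobody knows whether the new drug will be tolerated. A switch arm conditioned on having reached valproate reduction describes a selected group. The results are meant to supply the personal-risk figures in a national decision support tool (Pathways to impact).

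**Working it through.** **1. The plan's own figures.** Table 1 uses p1 = 2977/8021 = 0.371 (withdrawn) and p2 = 2471/8021 = 0.308 (remaining), a difference of 0.063. The printed formula, (z for 0.975 + z for 0.80)² × [p1(1−p1) + p2(1−p2)] / (p1−p2)², reproduces 881. This figure does not bear on the point. The Introduction says that the pilot grouped everyone withdrawn, whether or not switched, so the documents contain no switch-arm risk.

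**2. Trace one patient.** The patient starts lamotrigine or levetiracetam, later stops it, and never reduces valproate.

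| Rule in the article | What happens to this patient |
|---|---|
| Target trial design | Assigned to the switch while on valproate; events count from assignment until deviation |
| Time 0 at dose reduction | Never enters arm 1 or 2 |
| Time 0 at discontinuation | Never enters arm 1 or 2 |
| Arm 4, matched time | Not barred. An event after the matched date counts for arm 4 unless starting the new drug is treated as deviation, which is not stated. An event before it is no arm's outcome |
| Baseline adjustment | Acts on those who entered an arm; cannot restore someone who did not |
| Censoring at deviation | Same |

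Choosing either stated date leaves the result unchanged for this patient. Choosing discontinuation also puts the taper before follow-up.

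**3. Direction.** Let R be the risk among all starters of the new drug, f the share who never reduce valproate, and q the risk in that share. The risk seen in the switch arm is

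(R − f·q)/(1 − f),

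so observed minus true = f(R − q)/(1 − f). The sign depends only on whether q is above or below R. With q = kR, the observed/true ratio is (1 − fk)/(1 − f).

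Both f and k are assumptions, since the documents give neither:

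| f | k = 0.5 | k = 1 | k = 1.5 | k = 2 |
|---|---|---|---|---|
| 5% | 0.975/0.95 = 1.03 | 1.00 | 0.925/0.95 = 0.97 | 0.90/0.95 = 0.95 |
| 10% | 0.95/0.90 = 1.06 | 1.00 | 0.85/0.90 = 0.94 | 0.80/0.90 = 0.89 |
| 15% | 0.925/0.85 = 1.09 | 1.00 | 0.775/0.85 = 0.91 | 0.70/0.85 = 0.82 |

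Harmed patients who return to valproate alone correspond to k above 1. Patients who do well on both drugs and stay on both correspond to k below 1. Neither group enters arm 1 or 2. The table shows that the sign can go either way; it is not an estimate for this study.

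**The case against.** The article does not say whether the new drug is introduced before, with or after valproate reduction. If it is never first, nothing is lost under the dose-reduction date. This stands: the point is conditional on that order, which the article neither states nor excludes.

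A reader might infer that arms 1 and 2 admit only completed withdrawals. The arm labels and the discontinuation date suggest it, but Treatment assignment places patients at the start of reduction and follow-up censors deviation. A taper begun and reversed can therefore be read as entered and then censored. Only those who never begin a reduction are excluded under both readings.

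A reader might also argue that a failed switch should count throughout follow-up for the arm assigned. That is the intention-to-treat effect. The emulation keeps a per-protocol estimand, so only events up to the point of giving up the new drug would count.

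A size is tempting too. Giving 5–15% of starters 1.5–2 times the 30.8% pilot risk yields an excess of 0.05 × 0.5 × 30.8 = 0.8 to 0.15 × 1 × 30.8 = 4.6 points, or 12–73% of the 6.3-point pilot difference. The documents do not support this. It applies a risk from a 5-year analysis to patients who would be censored early, takes both multipliers from assumption, and divides by a contrast that is not a switch contrast.

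Finally, grace periods and overlap rules may sit in a fuller document. That is fair for the detail. But the article itself fixes time 0, twice and differently, and both versions leave out the start of the new drug.

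**Conclusion.** The point holds in conditional form. Both stated time-0 dates depend on valproate alone and contradict each other. Where lamotrigine or levetiracetam is started first, events during its introduction fall before follow-up. Patients who abandon it without reducing valproate never enter a switch arm and may be counted in arm 4. The stated adjustment and censoring do not repair this.

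Neither direction nor size can be derived from the documents. A reader might infer that switching will necessarily look too safe, or that the lamotrigine–levetiracetam ranking will be distorted. The first needs the excluded patients to be at higher risk than other starters. The second needs the selection to differ between the drugs. The article gives no data on either. The conclusion rests on one assumption, that some patients start the new drug before reducing valproate. It matters because the emulated trial and the prediction model both address people who have not yet begun to withdraw.

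**What to change.** 1. Reconcile Treatment assignment with Start and end of follow-up, so that arms 1–3 have one time 0.
2. Add a prespecified analysis, at minimum a sensitivity analysis beside the dose-reduction analysis. In it, time 0 for the switch strategies is the earlier of the first new prescription of lamotrigine or levetiracetam (no prior use) and the first valproate reduction.
3. In that analysis, allow a fixed analytic grace period for withdrawal. Clone each patient into the strategies compatible at time 0, censor a clone when it deviates, and weight for that censoring.
4. Define the arm 4 strategy there as continuing valproate without starting either drug. Otherwise a patient who has just started one is compatible with both strategies, and the same lead-in event is credited to each.
5. Measure baseline covariates before that date, so that the new drug and events on it do not become adjustment variables.
6. Report, by drug, how many start it and never reduce valproate. This supplies the share that the documents lack.

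The cost is protocol wording and programming. Study status and timeline says that data access is still being sought, so this can be settled before extraction. The downside is that some patients who add the drug with no intention of leaving valproate contribute time until the grace period ends, which is why the dose-reduction analysis is kept alongside.

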## Introduction

Epilepsy impacts 70 million people worldwide [1]. Valproate is one of the most effective drugs for treating epilepsy, outperforming any other in idiopathic generalised epilepsy, which affects a third of people with epilepsy (PWE) [2,3]. It was the most prescribed antiseizure medication (ASM) globally in the early 2000s [4]. However, widespread evidence demonstrating foetal congenital malformations (11%) and neurodevelopmental disorders (30–40%) associated with prenatal valproate exposure led to guidance changes between 2015–2018 [5]. These prohibited valproate prescribing in women of childbearing potential unless other ASMs had failed, subsequently halving prescriptions in women [4,5].

Valproate remains the first-line ASM for men with newly diagnosed generalised epilepsy in most countries [2,3]. In the UK, regulators recently considered valproate’s known risks of impaired male fertility, emerging pre-clinical evidence of transgenerational risks with prenatal exposure, and animal studies suggesting adverse effects on testes [5,6]. In response, they announced a phased implementation (from January 2024) of recommendations restricting valproate prescribing for both men and women aged <55 years unless other ASMs have failed [5,6]. Similar restrictions are being considered in other countries [7–9]. Together, they are likely to result in withdrawal of valproate from a substantial number of men already taking it, as has been the case for women [4,5].

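### Calendar date of time 0 is not among the named candidate confounders, and the matched-time rule for arm 4 does not say whether it supplies it

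*Protocol article*

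**What the plan says.** All places are in the Protocol article.

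- **Window.** Under the eligibility criteria: "The study period will be from 01/01/2014 to 01/01/2024". The cohort is open, so time 0 falls on different dates for different patients.
- **Covariates.** Under treatment assignment the list opens "considering age, sex, ethnicity, deprivation, type of epilepsy (using G40 codes), baseline seizure frequency (symptom codes recorded over preceding 12 months" and closes "alcohol excess, developmental delay, Cambridge Multimorbidity Score, length of valproate treatment, valproate dose, and ASMs used other than valproate". That is six plus six, twelve in all.
- **Status of the list.** The next sentence reads "The final set of covariates required to adjust for confounding will be chosen using a causal directed acyclic graph".
- **Time 0 for continuers.** Both the treatment-assignment text and the follow-up text give "prescription of valproate at a matched time (arm 4", without a scale or a statement of which withdrawal arm supplies the match.
- **Aim 1 contrast.** The causal estimand "Assesses impact of treatment arms 1–3 vs. 4 on outcome".
- **Policy background.** The Introduction says that evidence of harm from prenatal exposure "led to guidance changes between 2015–2018", "subsequently halving prescriptions in women".
- **Aim 2.** The prediction model is to give a patient's risk on levetiracetam and on lamotrigine side by side. Candidate predictors come from the Aim 1 confounder list, plus variables that influence the outcome but not treatment assignment.

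**The concern.** By the protocol's own account, the pressure to leave valproate changed inside the study window. A woman withdrawn before the guidance may have come off for a different reason, and so with a different underlying risk, than one withdrawn after it. Calendar date is then a plausible cause of treatment assignment and, through the reason for withdrawal, of outcome. Sex is on the list, but a main effect of sex cannot represent a change over time within women. The pilot took withdrawals only from 01/06/2015 to 01/06/2018; the new design widens this to ten years without naming date as a covariate.

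Weights built from the twelve covariates do not balance date except as far as those covariates happen to track it. If the mix of switches also moved over the decade, some of the difference between eras would be read as a difference between drugs. The comparison most exposed is lamotrigine against levetiracetam in Aim 2, which is intended for a public decision tool.

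**Working it through.** **Reading the text.** Three questions settle how far the gap reaches.

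1. *Is date in the list?* No. None of the twelve items is index date, calendar year or regulatory era.
2. *Does the matched-time rule supply it?* Possibly, for arm 4 only. If matching is on calendar date within each withdrawal arm, arm 4 has the same date distribution as its comparator and this bias is zero in each Aim 1 contrast. If arm 4 is matched to the three withdrawal arms taken together, each separate contrast can remain unbalanced. If matching is on treatment duration or age, date is not controlled at all. The text does not choose between these.
3. *Can date enter Aim 2 another way?* Not by the wording. The extra-predictor route is described for variables that do not affect treatment assignment. A date effect that confounds does affect it, so its stated route in is the confounder list.

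**Size, by illustration.** The article gives no arm-by-year counts and no era effect, so every input here is an assumption. Suppose there is no true drug effect. Let the event rate be 1 in the earlier half of the window and r in the later half. Let a share a of one switch arm, and 1 − a of the other, enter in the earlier half.

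*Entry-share formula:* arm rate = (early share × 1) + (late share × r).

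| r | a = 60% | a = 70% |
|---|---|---|
| 1.2 | 1.12/1.08 = 1.037 | 1.14/1.06 = 1.075 |
| 1.5 | 1.30/1.20 = 1.083 | 1.35/1.15 = 1.174 |
| 0.7 | 0.82/0.88 = 0.932 | 0.79/0.91 = 0.868 |

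With equal era mix the ratio is 1. If arm 4 were a 50/50 pool, its rate at r = 1.5 would be 1.25, and the two 70/30 arms would stand at 1.15/1.25 = 0.92 and 1.35/1.25 = 1.08 against it.

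*Correction for later person-time.* The formula above holds each patient at the rate of the entry period throughout. Follow-up runs for up to 10 years, so early entrants also live through the later half. Assume uniform entry within each five-year half and follow-up ending with the window. An early entrant then contributes on average 2.5 early and 5 late years; a late entrant contributes 2.5 late years. For r = 1.5 and 70/30:

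- Arm with 70% early: early years 0.7 × 2.5 = 1.75; late years 0.7 × 5 + 0.3 × 2.5 = 4.25; rate (1.75 + 4.25 × 1.5)/6 = 1.354.
- Arm with 30% early: early years 0.75; late years 0.3 × 5 + 0.7 × 2.5 = 3.25; rate (0.75 + 3.25 × 1.5)/4 = 1.406.
- Ratio 1.406/1.354 = 1.04, against 1.17 before.

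The same steps take the mildest case (r = 1.2, 60/40) to (5.2/4.5)/(6.3/5.5) = 1.01, and the r = 0.7, 70/30 case from 0.87 to (3.025/4)/(4.725/6) = 0.96.

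A hazard ratio by time since time 0 lies between the two calculations early on. In the worst case it is 1.174 at time 0. At 2.5 years it is (0.3 × 1.25 + 0.7 × 0.5 × 1.5)/0.65 = 1.385 in one arm over (0.7 × 1.25 + 0.3 × 0.5 × 1.5)/0.85 = 1.294 in the other, or 1.07. By five years it is 1.

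**Which calculation applies.** The correction is right if the era acts on events as they occur, for example through recording or service use. If the era acts through who was withdrawn and why, the effect stays with the patient and the entry-share figures are the relevant ceiling.

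**The case against.** The strongest reply is that no weight model is fixed here. The list is introduced as covariates to be considered, the final set is to come from a causal graph, and a condensed article may leave that set to a fuller document. This stands: it is not established that date will be absent from the final adjustment, and a reader who infers that the trial will ignore calendar time goes beyond the text.

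Several other strong readings also fail:

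- *That every arm-versus-continuation contrast is biased.* This needs arm 4 to be matched to the pooled withdrawal arms. The article does not say pooled, and matching within each arm fits the wording equally well.
- *That Aim 1 treats the three withdrawal arms as contemporaneous.* The Aim 1 estimand compares each with arm 4. Only Aim 2 sets the switch arms against each other.
- *That coding practice changed over the decade, or that the choice between lamotrigine and levetiracetam drifted.* Neither is documented. The reported guidance concerns stopping valproate in women, not which drug replaced it. The Introduction does not say in which countries the 2015–2018 changes applied, while the Aim 2 model is developed in a mainly US source.
- *That the January 2024 restriction adds a second shift.* It begins as the window closes.
- *That the bias rivals the planning effect.* Table 1's ratio, 2977/2471 = 1.20, is withdrawn against continuing, not one switch arm against another.

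What remains is that a policy shift described in the Introduction has no counterpart in a list of twelve otherwise specific covariates, and that the one device that might cover it is undefined and cannot reach arms 1 to 3 among themselves.

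**Conclusion.** The point holds as an inexpensive improvement to the stated plan, not as a demonstrated error. Index date is missing from the named candidates, despite a ten-year window that contains a policy change the protocol itself reports. The Aim 1 contrasts are largely protected if arm 4 is date-matched within each withdrawal arm, but the text does not commit to that. The Aim 2 comparison of lamotrigine with levetiracetam has no stated protection.

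The direction and size of any bias are unknown. Under the assumed mixes and no drug effect, the entry-share ratios for higher later rates are 1.04 to 1.17. The real figure is probably smaller, because early entrants also accrue later person-time: the crude rate ratios become 1.01 to 1.04. If the switch arms have the same spread of index dates, the bias from this source is nil.

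**What to change.** 1. Add the calendar date of time 0 to the causal graph and to the weight model for all four arms, in flexible form (a spline or year terms), with a date-by-sex interaction because the reported guidance concerned women.
2. Define the matched time for arm 4 as calendar date, matched within each withdrawal arm.
3. Carry index date into the confounding adjustment of the Aim 2 model, so that the two drugs are compared within the same period.
4. Tabulate index year by arm before any outcome is examined, to show whether the arms differ in era at all.

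Index date follows from the definition of time 0 and so exists for every patient; no new data are needed. The cost is somewhat more variable weights in years where an arm is sparse.
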